## **32. Privacy and Confidentiality of Subjects**

The storage, use, and confidentiality measures of subjects' personal information will be truthfully informed to the subjects, and their personal information will not be disclosed to third parties without authorization; there are confidentiality measures for subjects' personal information and related materials. This study has established a strict subject management system to ensure the rights and safety of subjects. All subjects are required to sign an informed consent form to fully understand the content of the study, potential risks, and the right to withdraw. During the study, subjects will be closely monitored by professional medical staff, and any discomfort or adverse reactions will be promptly handled and recorded. The research team will regularly communicate with subjects and their families to ensure their understanding of the study progress and participation.

### **33. Publication or Disclosure of This Study's Results**

Regardless of the outcome, we will endeavor to publish the results of this study. Data management will follow strict standard operating procedures to ensure the accuracy, integrity, and confidentiality of the data. Data collection will be completed by an independent nurse data collector, and all data will be cross-verified by two researchers after collection to ensure accuracy before being entered into the system. All original data and records will be retained for five years after the study ends for subsequent audits and verification. Under the management of the ethics committee and the department, a data safety monitoring committee will be established for this study, composed of experts in statistics, clinical practice, and ethics. Its responsibilities include regularly reviewing the study progress, subject safety, and adverse events to ensure the scientific and compliant nature of the study. Meetings will be held once during the middle and once at the end of the study to review the data and provide suggestions.

### **34. Implementation Conditions and Researchers of This Study**

(1) Whether the Study Site and Equipment Conditions Can Meet the Needs of the Study Tasks:

Study Site: Department of Critical Care Medicine, Affiliated Hospital of Zunyi Medical University.

Equipment Conditions: Ultrasound.

(2) Whether the Qualifications, Experience, and Technical Abilities of the Researchers Meet the Requirements of the Study:

This study relies on the Affiliated Hospital of Zunyi Medical University, which is a direct affiliated hospital of Zunyi Medical University, a university co-built by the National Health Commission (formerly the National Health and Family Planning Commission) and the People's Government of Guizhou Province. The predecessor of the hospital was the Affiliated Hospital of Dalian Medical University, which was relocated to Guizhou in 1969 to support the construction of the third line. It is the first tertiary general hospital in Guizhou Province and also the diagnosis and treatment center for severe acute pancreatitis in Guizhou Province. The department has anesthetists who have been engaged in critical care medicine for many years, which means that they have accumulated certain professional knowledge and skills in the relevant fields and can quickly adapt to and master new technologies, providing a solid technical basis for the smooth implementation of the project. The team has a reasonable personnel structure and rich clinical and research experience, which can provide a solid foundation for this study.

(3) Whether the Medical Practice Qualifications and Experience of the Researchers Can Ensure the Safety and Medical Care of the Subjects:

The research team consists of 14 members, including 2 project managers, 2 anesthesiologists, 3 clinical physicians,

5 pain management nurses, and 2 data collection researchers. Project managers are responsible for pain management training, nurse capability assessment, and study implementation supervision. Anesthesiologists are responsible for epidural catheter placement and analgesic plan adjustment. Clinical physicians manage the daily medical care of patients and participate in plan adjustments. Pain management nurses implement pain assessment and analgesia based on the symptom management theory, record pain scores and adverse reactions. Data collection researchers are responsible for data collection, organization, quality control, and analysis, using GraphPad Prism software to ensure the scientific nature of the results. Three members have hosted or participated in three provincial and municipal scientific research projects, published several papers, and applied for more than 10 patents. The team members have rich clinical work experience and are proficient in the diagnosis, treatment, and nursing processes of various SAP patients.

(4) Whether There Are Qualified Researchers or Researchers Trained to Obtain Informed Consent and Provide Consultation on Safety Issues at Any Time:

[name], one of the researchers in this project, has long been engaged in the clinical and research work of the Department of Critical Care Medicine. All members of the research team hold professional qualification certificates for physicians or nurses in their respective fields.

(5) Division of Labor Among Researchers:

Project Managers: Responsible for pain management training, nurse capability assessment, and study implementation supervision.

Anesthesiologists: Responsible for epidural catheter placement and analgesic plan adjustment.

Clinical Physicians: Manage the daily medical care of patients and participate in plan adjustments.

Pain Management Nurses: Implement pain assessment and analgesia based on the symptom management theory, record pain scores and adverse reactions.

Data Collection Researchers: Responsible for data collection, organization, quality control, and analysis, using GraphPad Prism software to ensure the scientific nature of the results.

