## 9. Research team and implementation process

The study team consisted of 14 multidisciplinary members, including two project managers, two anesthesiologists, three ward clinical physicians, five pain management nurses, and two data collection researchers.

The project manager was responsible for the training and supervision of the pain management strategy to ensure that the nurses were competent in implementing the strategy and meeting the requirements of the study protocol. The anesthesiologist was responsible for epidural placement, providing technical support to ensure patient comfort and safety, and assisting in the development of the analgesic protocol. The ward clinical physicians were responsible for the daily medical management of patients, handling emergencies, ensuring patient safety, and participating in the development and adjustment of the pain management program. Pain management nurses, based on SMT, lead the implementation of pain assessment and management strategies for SAP patients in the ICU, record pain scores, perform TEA drug administration, handle patients' pain feedback, closely observe pain responses, communicate with physicians in a timely manner, ensure effective implementation of the pain management program, and record adverse reactions. The data collection researcher is responsible for collecting study data, including pain scores and adverse events, ensuring data accuracy and completeness, performing data quality control and analysis, using professional statistical software to analyze the data, and providing data analysis reports to ensure the scientific and rigorous nature of the study results. The implementation process includes: 1. patient screening and enrollment: screen patients who meet the criteria, obtain informed consent, and randomize the group; 2. pain assessment: use VAS to assess pain and record scores; 3. epidural placement: anesthesiologists perform placement and ensure safety; 4. implementation of analgesic program: the control group uses continuous

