## 14. Blinding

Because this is an interventional study, pain management nurses will not be aware of the specific grouping of patients until after they begin to implement the intervention, but they will not be involved in other parts of the study. Although there are measures that can be taken to try to keep patients blinded to subgroups, there are still difficulties in avoiding exposure altogether. For this reason, data collectors and data analysts will remain blinded to the specific intervention protocols, and independent persons who are not aware of the specific intervention protocols will be responsible for data collection and analysis, thus ensuring that data collectors and statistical

analysts are blinded to the treatment assignment and minimizing potential bias in data processing and analysis.

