## **20.Secondary outcomes**

Intra-abdominal pressure (IAP): Measured by trans cystic intra-abdominal pressure measurement method. Specific operation is: the patient lying position, after indwelling catheter connected to the tee and pressure measuring tube, after draining the urine clamped closed urinary catheter, through the urinary catheter into the bladder 25 °C ~ 35 °C 25 ml of sterile saline, measuring tape aligned with the iliac crest axillary midline as the zero adjustment, when the liquid plane in the pressure measuring tube is no longer falling, in the end of the patient's exhalation, the scale number of the concave surface of the liquid surface in the pressure measuring tube to the scale number of the pressure is the intra-abdominal pressure. Measurement time and personnel are the same as the VAS-P.

Number of additional interventions (NAI): the number of additional interventions given by the pain management bedside nurses to patients with VAS-P greater than 3 or intolerable pain after continuous TEA in the control group and experimental group. The total number of interventions was recorded on Day1, Day2, and Day3, respectively.

Dosage of combined drugs (DCD): the total amount of combined drugs (nalbuphine 40 mg + ropivacaine 225 mg + lidocaine 0.2 g + 0.9% saline 6 ml, totaling 50 ml) during epidural placement.

Number of days of epidural placement (NDEP): calculated by the data collection researcher from the start of insertion to the time of extubation.

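### The blinding section excludes the arm-aware nurses from data collection, yet other sections have them record pain scores and the drug-related adverse events; the blinding of collection and analysis has no stated safeguard

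*Protocol*

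**What the plan says.** Protocol Section 14 (Blinding) makes three statements.

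- On the nurses' knowledge: "pain management nurses will not be aware of the specific grouping of patients until after they begin to implement the intervention".
- On their role, directly after: "but they will not be involved in other parts of the study".
- On everyone else: "data collectors and data analysts will remain blinded to the specific intervention protocols". It assigns both tasks to people who stand outside the intervention and do not know the arm.

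Other sections describe the same roles differently.

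- Section 9 has the pain management nurses "record pain scores, perform TEA drug administration". Section 34 repeats that they "record pain scores and adverse reactions".
- Section 21 names these nurses as the people who observe and record the drug-related adverse events.
- Section 19 gives the VAS-P at 0, 1, 6, 12, 24, 48 and 72 h to the data collectors. Section 20 says of intra-abdominal pressure (IAP): "Measurement time and personnel are the same as the VAS-P".
- Sections 9 and 34 give the two data collection researchers both ends of the work. In Section 34 they are "responsible for data collection, organization, quality control, and analysis".
- Section 33 speaks of one independent nurse data collector, and Sections 23 and 33 require a cross-check by two researchers before data entry.

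**The concern.** Section 14 concedes that patients are hard to keep blinded. Blinding of collectors and analysts is then the main protection against bias that the protocol offers, so the role descriptions have to agree with it.

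For the nurses they do not agree. Someone who gives the epidural drug and knows the arm also records whether hypotension, itching or nausea followed. Adverse events are a secondary outcome (Section 6) and carry the safety hypothesis that the experimental arm has no higher incidence (Section 7). A reader who trusts Section 14 would take that comparison as blinded.

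For the collectors and analysts the weakness is different. One pair of people collects, checks and analyses, so anything that shows them the arm at the bedside goes with them into the analysis. IAP is read by eye from a liquid column. Section 24 lets the choice of test depend on the distribution and leaves part of the missing-data handling to be decided case by case. Such choices need an analyst who does not know the arm.

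**Working it through.** No figure in the protocol bears on this point, so the check sets the role statements side by side.

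**1. Nurses.**

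| Question | Section 14 | Elsewhere |
|---|---|---|
| Do they know the arm? | Yes, once the intervention begins | Section 17: they deliver the arm-specific strategy in the experimental group |
| Do they record study data? | No: no other part, and collection is by unaware independent persons | Yes: pain scores and adverse reactions (Sections 9, 34); drug-related events (Section 21) |

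The second row cannot be reconciled for the drug-related events. Section 21 names no other recorder for them. By the protocol's own count they are 8 of the 8 + 8 = 16 events. The other eight, the puncture-related events, are recorded by healthcare workers whose knowledge of the arm is not described.

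**2. The primary outcome.** Section 19 assigns the timed VAS-P to the data collectors. Sections 9 and 34 have the nurses record pain scores, and the listed implementation steps in Section 9 do not say who scores. Nurses need a score because a VAS-P above 3 prompts an additional intervention (Section 17). Two records may therefore exist for one patient. No section says that only the collectors' record enters the analysis.

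**3. Collection and analysis in one role.** The team is 2 project managers + 2 anesthesiologists + 3 physicians + 5 pain nurses + 2 data collection researchers = 14, with no separate statistician. Section 14 gives collection and analysis alike to unaware persons. One role doing both is consistent with that. What follows is conditional: if collection shows the arm, the analysis is unblinded as well.

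**4. Can collection show the arm?** The outcome totals need not. The number of additional interventions (NAI) is a daily count kept in both arms, and the combined drug dosage (DCD) is a total amount. The entries behind them do differ. Under Section 17 an additional intervention is a pump rate step of 1-2 ml/h in the control arm and a 5 ml epidural injection in the experimental arm. Section 20 does not name who compiles NAI or DCD. Section 9 makes the data collection researcher responsible for collecting study data in general. Collectors also visit up to 72 h after placement and ask about satisfaction on the day of catheter removal. No section describes masking of the pump, the chart or the data file.

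**The case against.** The strongest reply is that Section 14 can be honoured as it stands. It gives collection and analysis to unaware people, Section 19 gives the timed VAS-P to the data collectors, and Section 33 calls the collector independent. The nurses' scores are naturally read as trigger scores only. Recording drug reactions can be seen as part of safe administration. The patient marks the VAS-P line, so the collector does not rate pain, and IAP is read under a fixed zero and end-expiration rule.

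Much of this stands, and it rules out several stronger readings that a reader might draw.

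- *That a joint collector and analyst role contradicts the blinding.* It does not, because Section 14 assigns both tasks to unaware persons.
- *That NAI, DCD and adverse-event totals reveal the arm.* They are defined identically in both arms. Only the source entries differ, and no section says that the collectors see them.
- *That the primary VAS-P is taken by the treating nurses.* Section 19 says otherwise. The gap is that the protocol does not exclude the nurses' record.
- *That all outcomes are exposed to assessor bias.* A patient-marked scale and 28-day mortality leave an assessor little room.

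The reply does not rescue the drug-related adverse events. They are analysed as an outcome, their named recorder knows the arm, and Section 14 says that such a person collects no data.

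**Conclusion.** The blinding statement is wrong for the drug-related adverse events, unsettled as to which VAS-P record is analysed, and unprotected for collection and analysis as a whole. The documents do not show that collectors or analysts will know the arm. They show that nothing described would prevent it, and that the analysis would share any unmasking that happened at the bedside.

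The conclusion for the adverse events rests on the text alone. The conclusion for collection and analysis rests on the inference that a collector may meet the pump and injection entries, which is plausible but not stated. Neither the size nor the direction of any bias can be computed from the protocol. The matter should be settled before the data are analysed. Both the blinding claim and the division of labour are fixed in the protocol, so it cannot be left to a separate analysis plan.

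**What to change.** 1. Reconcile Sections 9, 14, 19, 21, 33 and 34. State that only the VAS-P taken by the data collectors at the set time points enters the primary analysis, and that nurse scores serve only to trigger additional analgesia.
2. Limit the claim in Section 14: say that drug-related adverse events are recorded unblinded by the treating nurses.
3. Have the staff who hold the allocation list (Section 13) supply a data file with arms coded A and B. Analyse VAS-P, IAP and satisfaction from it before NAI, DCD and adverse-event data are merged. Keep the two-researcher cross-check. Dividing the variables between the two researchers is not proposed, because it may clash with that check.
4. If collectors cannot be kept from the pump and injection records, report collection as unblinded and state that the same people ran the analysis. A coded file does not help an analyst who already knows individual patients' arms.

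The cost is a little extra data handling by existing staff and a less favourable blinding statement.

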### **35. SPIRIT-Figure**

SPiRiT-Figure:Schedule of enrolment, interventions and assessments

|                                                  | STUDY PERIOD    |            |                 |                |                |                |                |                |                |                |                |                |                |           |
|--------------------------------------------------|-----------------|------------|-----------------|----------------|----------------|----------------|----------------|----------------|----------------|----------------|----------------|----------------|----------------|-----------|
|                                                  | Enrolment       | Allocation | Post-allocation |                |                |                |                |                |                |                |                |                |                | Close-out |
| TIMEPOINT**                                      | -t 1 | 0          | t 1  | t 2 | t 3 | t 4 | t 5 | t 6 | t 7 | t 8 | t x | t y | t z |           |
| TIME                                             |                 |            | 0h              | 1h             | 3h             | 6h             | 12h            | 24h            | 48h            | 72h            |                |                |                |           |
| ENROLMENT:                                       |                 |            |                 |                |                |                |                |                |                |                |                |                |                |           |
| Eligibility screen                               | X               |            |                 |                |                |                |                |                |                |                |                |                |                |           |
| Review inclusion and exclusion criteria          | X               |            |                 |                |                |                |                |                |                |                |                |                |                |           |
| Informed consent                                 | X               |            |                 |                |                |                |                |                |                |                |                |                |                |           |
| Allocation                                       |                 | X          |                 |                |                |                |                |                |                |                |                |                |                |           |
| Randomization Blinding                           |                 | X          |                 |                |                |                |                |                |                |                |                |                |                |           |
| INTERVENTIONS:                                   |                 |            |                 |                |                |                |                |                |                |                |                |                |                |           |
| [Control group]                                  |                 |            |                 |                |                |                |                |                |                |                |                |                |                |           |
| [Experimental group]                             |                 |            |                 |                |                |                |                |                |                |                |                |                |                |           |
| ASSESSMENTS:                                     |                 |            |                 |                |                |                |                |                |                |                |                |                |                |           |
| Sociodemographic information and clinical status | X               | X          |                 |                |                |                |                |                |                |                |                |                | X              |           |
| Visual Analog Scale for Pain(VAS-P)              |                 |            | X               | X              | X              | X              | X              | X              | X              | X              |                |                |                |           |
| Intra-abdominal pressure(IAP)                    |                 |            | X               | X              | X              | X              | X              | X              | X              | X              |                |                |                |           |
| Number of additional interventions(NAI)          |                 |            |                 |                |                |                |                | X              | X              | X              |                |                |                |           |
| Dosage of combined drugs(DCD)                    |                 |            |                 |                |                |                |                |                |                |                | X              |                |                |           |
| Number of days of epidural placement(NDEP)       |                 |            |                 |                |                |                |                |                |                |                | X              |                |                |           |
| Puncture-related adverse events                  |                 |            |                 |                |                |                |                |                |                |                |                |                |                |           |
| Drug-related adverse events                      |                 |            |                 |                |                |                |                |                |                |                |                |                |                |           |
| Puncture surgery rate (PSR)                      |                 |            | X               |                |                |                |                |                |                |                |                |                |                |           |
| Length of stay in ICU (ICU-LOS)                  |                 |            |                 |                |                |                |                |                |                |                |                | X              | X              |           |
| 28-day mortality rate (28D-MR)                   |                 |            |                 |                |                |                |                |                |                |                |                | X              | X              |           |
| Satisfaction score with analgesic effect (SAE)   |                 |            |                 |                |                |                |                |                |                | X              |                |                |                |           |

tx: Remove the thoracic epidural catheter

ty and tz: transfer out of the ICU or be admitted to the ICU for 28 days.

Figure 5:SPiRiT-Figure:Schedule of enrolment, interventions and assessments
